## Abstract

**Background:**

In North America, although it varies according to the specific type of acute respiratory infections (ARI), use of antibiotics is estimated to be well above the expected prevalence of bacterial infections. The objective of this pilot clustered randomized controlled trial (RCT) is to assess the feasibility of a larger clustered RCT aiming at evaluating the impact of DECISION+, a continuing professional development (CPD) program in shared decision making, on the optimal use of antibiotics in the context of ARI.

**Methods/design:**

This pilot study is a cluster RCT conducted with family physicians from Family Medicine Groups (FMG) in the Quebec City area, Canada. Participating FMG are randomised to an immediate DECISION+ group, a CPD program in shared decision making, (experimental group), or a delayed DECISION+ group (control group). Data collection involves recruiting five patients consulting for ARI per physician from both study groups before (Phase 1) and after (Phase 2) exposure of the experimental group to the DECISION+ program, and after exposure of the control group to the DECISION+ program (Phase 3). The primary outcome measures to assess the feasibility of a larger RCT include: 1) proportion of contacted FMG that agree to participate; 2) proportion of recruited physicians who participate in the DECISION+ program; 3) level of satisfaction of physicians regarding DECISION+; and 4) proportion of missing data in each data collection phase. Levels of agreement of the patient-physician dyad on the Decisional Conflict Scale and physicians' prescription profile for ARI are performed as secondary outcome measures.

**Discussion:**

This study protocol is informative for researchers and clinicians interested in designing and/or conducting clustered RCT with FMG regarding training of physicians in shared decision making.

**Trial Registration:**

ClinicalTrials.gov Identifier: NCT00354315

## Background

Most health decisions occur in context of scientific uncertainty, the "grey zone" of decision making, and making decisions about the use of antibiotics for acute respiratory infections (ARI) is no exception [1]. ARI are the most frequently reported reasons for consulting a primary care provider in North America and include acute otitis media, acute rhinosinusitis, acute pharyngitis, and acute bronchitis. Together, these infections, excluding pharyngitis but including chronic sinusitis and eustachian tube disorders account for 5.7% of the primary diagnosis groups for adults and reach a total of 16.3% for children under the age of twelve in community based practices [2]. Although each type of ARI has distinct features, they all share in common that a large proportion of those infections are viral. Indeed, only 38% of adults with rhinosinusitis, 6% to 18% of children with ARI, and 5 to 15% of adults with pharyngitis have a bacterial infection [3,4]. Nonetheless in North America, although it varies according to the specific type of ARI [5-13], the use of antibiotic is estimated to be 63% to 67%, well above the expected prevalence of bacterial infections [5,7-11,14-17].

As suggested above, diagnostic and management of ARI are ripped with uncertainty. The probabilistic nature of the diagnosis of ARI makes it difficult for both the physician and the patient to choose the "best" course of action and is associated with prescription of antibiotics [18]. Scientific evidence that imparts conflicting results regarding treatment options (i.e. balance between risks and benefits) or the absence or insufficiency of scientific evidence makes this choice even more difficult [19]. Moreover, the probabilistic aspect of the evidence that is drawn from populations implies uncertain outcomes for the individual [20]. Consequently, patients and physicians need help in addressing their decisional needs and in resolving uncertainty when making decisions about the use of antibiotics for ARI, the most frequent "grey zone" health decisions in primary care.

Shared decision making (SDM) is a promising strategy for effective knowledge translation (KT) between health providers and their patients, particularly so in contexts of "grey-zone" decisions [21]. SDM refers to a process by which a healthcare choice is made by practitioners together with the patient, based on the best available evidence and in line with what an informed patient would value. If indeed "Knowledge translation is the exchange, synthesis and ethically-sound application of knowledge – within a complex system of interactions", then conceptualizing and operationalizing it as an interactive and dynamic process between patients and health providers has important consequences. It may foster a new breed of more effective KT interventions in clinical contexts [22].

However, it is not clear how SDM can be implemented in clinical practice. Given that most current efforts in KT deal with the implementation of clinical practice guidelines (CPG) where recommendations are considered as rules to be followed, it is not clear if the implementation processes of SDM and CPG are compatible. The proposed study addresses the urgent need to reconcile the current KT endeavours with the need to determine effective ways by which patients are engaged to share their preferences and participate in the process to achieve "grey zone" decisions. In other words, it lays the grounds for a new KT model at the clinical level: the SDM model.

We are planning a large clustered randomized clinical trial (RCT) aiming at evaluating the impact of DECISION+, a continuing professional development program in shared decision making on the optimal use of antibiotics for treating ARI. We report on the study protocol of an ongoing pilot clustered randomized controlled trial (RCT) to assess the feasibility of this larger trial. Based on our conceptual framework (Figure 1), specific aims include to: 1) assess the feasibility of recruiting Family Medicine Groups (FMG), family physicians/general practitioners (FPs/GPs) and their patients, 2) develop, adapt and validate DECISION+ training workshops and related material, and 3) evaluate physicians' participation and satisfaction regarding DECISION+. Specific aims also include estimating the impact of DECISION+ on: 1) decision of both physicians and their patients regarding the use of antibiotics, 2) decisional conflict scores of both physicians and their patients as well as level of agreement between their decisional conflict scores, 3) prescription profile of antibiotics for ARI, 4) intention of physicians to implement SDM in their clinical practice, 5) intention of physicians to implement clinical practice guidelines on ARI, 6) scores obtained by physicians on a Script Concordance Test (SCT), and 7) decisional regret of patients.

**Figure 1 F1:**
[figure not shown]
Decision+ Conceptual Framework.

## Methods/Design

### Design

The study is a two-arm clustered RCT conducted in the Quebec City area, Canada (Figure 2). FMG is the unit of randomisation. A FMG consists in a group of family physicians who work in close cooperation with nurses to offer family medicine services to registered individuals. There are currently over 130 such groups in the Province of Quebec. FMG are randomized to either 1) an immediate DECISION+ program (experimental group) or 2) a delayed DECISION+ program (control group). Simple randomisation and concealed assignment is performed by an independent biostatistician using Internet-based software.

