### Participants

#### Physicians

FPs/GPs are the main target participants and are recruited through FMG. A random list of all FMG in the Quebec City area was generated. Based on that list and in sequence, each physician who is in charge of the FMG is contacted by phone by one of the two co-principal investigators (FL or ML). If the contacted FMG includes at least 10 physicians, the study protocol is explained to the physician in charge and willingness to organise a meeting with colleagues from his/her group to further explain the nature of the project is sought.

FPs/GPs are not eligible to participate if they are currently participating or have previously participated to an implementation study of SDM in clinical practice. They are also excluded if they do not plan to be in clinical practice for the whole duration of the study (e.g. pregnancy, retirement, practice restricted exclusively to administrative duties). A FMG is not eligible if less than six eligible physicians agree to participate in the study. Reasons for exclusion or refusal to participate after the first telephone contact or after the face-to-face meeting are documented.

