### Sample size and analysis

The objective is to recruit four FMG (at least 24 physicians and a total of 360 patients with an ARI that is 5 patients per physician in each one of the three recruitment phases) for this pilot clustered RCT. This study is a feasibility study and therefore no sample size calculation was performed. Our design allow a comparison of physicians (and patients) data randomly exposed or not to the DECISION+ program (RCT) and a comparison of before and after data combining the results of the immediate and delayed exposure to the DECISION+ program.

It is not possible to blind participating FPs/GPs from the planned intervention but individuals involved with data analyses will be blinded to group allocation and initial results will be provided to researchers without revealing group allocation. Statistical analysis for the primary outcome feasibility measures will be performed using proportions and means and associated 95% confidence intervals. Methods for assessing the statistical significance of the secondary outcome measures between study groups will take into account the clustered nature of the dataset.

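### Simple randomisation of only four Family Medicine Groups leaves a substantial chance of an empty or single-practice arm; one restricted draw would remove it

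*Protocol article*

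**What the plan says.** Under Design, the protocol article describes a two-arm cluster trial and states that "FMG is the unit of randomisation". The arms are defined as follows: "FMG are randomized to either 1) an immediate DECISION+ program (experimental group) or 2) a delayed DECISION+ program (control group". The method is then given in one sentence: "Simple randomisation and concealed assignment is performed by an independent biostatistician using Internet-based software". The text mentions no blocking, pairing, stratification, minimisation or re-draw rule, and gives no allocation ratio or number of FMG per arm.

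Under Sample size and analysis, the target is set: "The objective is to recruit four FMG (at least 24 physicians and a total of 360 patients with an ARI". The same section foresees a randomised comparison of exposed with unexposed physicians and patients, significance tests of secondary outcomes between the groups that allow for clustering, and a before-after comparison that pools both groups.

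Under Data collection process, Phase 2 is timed from the third workshop of the immediate group and Phase 3 from the third workshop of the delayed group.

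**The concern.** Simple randomisation, in its ordinary technical sense, assigns each unit independently. Over many units the arms even out. Over four units they often do not, and nothing in the described method prevents all four FMG from landing in the same arm.

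Three things depend on how the four FMG fall:

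- **The randomised comparison.** If one arm is empty, there is no concurrent contrast and the planned between-group tests of the secondary outcomes cannot be done.
- **The data collection calendar.** With no immediate group, Phase 2 has no defined start. With no delayed group, Phase 3 has none. One primary feasibility measure, missing data, is defined by phase, so an empty arm touches it too.
- **The meaning of the contrast.** If one arm is a single FMG, the effect of DECISION+ is largely confounded with whatever is particular to that practice, and the between-FMG variance in that arm cannot be estimated.

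A pilot for a larger cluster trial should also try out running immediate and delayed groups side by side, which an empty arm would not allow.

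**Working it through.** **Inputs**

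- Units randomised: 4 FMG (Sample size and analysis), with the FMG as the unit (Design).
- Arms: 2 (Design).
- Method: simple randomisation, no restriction named (Design).
- Probability per arm: not stated. Assumed p = 0.5, with 0.4 and 1/3 as sensitivity values.
- Physicians per FMG: at least 6, from "A FMG is not eligible if less than six eligible physicians agree to participate in the study".
- Patients: "5 patients per physician in each one of the three recruitment phases".

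**Step 1. The plan's own figures.** 4 FMG × 6 physicians = 24 physicians. 24 × 5 patients × 3 phases = 360 patients. Both agree with the article, which confirms that four is the number of units the method must handle.

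**Step 2. Distribution of the split.** Under independent assignment, the number of FMG in the immediate arm is Binomial(4, p):

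- P(2:2) = 6p²(1−p)²
- P(3:1 either way) = 4p³(1−p) + 4p(1−p)³
- P(empty arm) = p⁴ + (1−p)⁴

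| p | 2:2 | 3:1 either way | empty arm |
|---|---|---|---|
| 0.5 | 6/16 = 37.5% | 8/16 = 50% | 2/16 = 12.5% |
| 0.4 | 34.6% | 49.9% | 15.5% |
| 1/3 | 29.6% | 49.4% | 21.0% |

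At p = 0.5, an arm holds at most one FMG with probability 50% + 12.5% = 62.5%. Of the two alternatives tried, both make a 2:2 split less likely and an empty arm more likely.

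**Step 3. Dependence on the number of units.** At p = 0.5 the chance of an empty arm is 2/2ⁿ. This gives 12.5% for n = 4, 3.1% for n = 6 and 0.8% for n = 8. The problem is specific to very few clusters.

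**Step 4. Precision at 3:1.** Assuming equal variance per FMG, the variance of the difference in FMG means is proportional to 1/n₁ + 1/n₂.

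- 2:2: 1/2 + 1/2 = 1.000
- 3:1: 1/3 + 1 = 1.333
- Ratio of standard errors: √(1.333/1.000) = 1.155, about 15% larger

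**Step 5. With two FMG per arm guaranteed.** There are C(4,2) = 6 equally likely allocations, so P(2:2) = 100% and P(empty arm) = 0%. The smallest two-sided permutation p-value at FMG level is then 2/6 = 0.33.

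**The case against.** Several points on the other side carry weight.

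- **No 2:2 target is written.** A reader might infer that the plan intends two FMG per arm and contradicts itself. The article does not support this, because it states no ratio. The point concerns what the named method can produce in a trial described as two-arm.
- **The word simple may be loose.** It could stand for an unstratified draw of two FMG out of four, in which case the problem disappears. The content of Figure 2 was not available to me, and a fuller protocol may say more. But the article does name a method, its plain meaning is unrestricted, and the text says nothing to narrow it. If a restricted draw was meant, one sentence is still needed.
- **The primary objective hardly depends on the split.** A reader might infer that the pilot as a whole is at risk. That goes too far. FMG recruitment, workshop attendance and satisfaction are not between-arm contrasts, and both groups receive DECISION+. The pooled before-after comparison also largely survives, even with one arm empty. The between-arm comparisons are secondary and exploratory, with no sample size calculation behind them.
- **The harm at 3:1 is partial.** Phase 1 is measured before exposure in both groups, so every FMG supplies its own baseline. Under a common between-FMG variance, 3:1 and 2:2 both leave 4 − 2 = 2 degrees of freedom. What is lost is the variance within the single-FMG arm, which has only 1 degree of freedom even at 2:2.
- **Restriction gains little power.** With four clusters and a minimum p-value of 0.33, the FMG-level test stays uninformative at 2:2.

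These points lower the severity. They do not answer the 12.5% chance that no randomised comparison exists.

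**Conclusion.** The point holds as a should-fix. As described, the allocation method suits four clusters badly: 37.5% for two per arm, 50% for a single-FMG arm and 12.5% for an empty arm. These figures are exact if FMG are assigned independently with probability 0.5, which is an assumption because the article gives no ratio.

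The damage falls on the randomised secondary comparisons, on the start of Phase 2 or Phase 3 and the missing-data measure tied to it, and on the pilot's value as a rehearsal of a two-arm cluster trial. The 15% loss of precision at 3:1 assumes equal variance per FMG and is minor in an unpowered pilot; the confounding of arm with practice matters more.

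Nor do the documents show that an unbalanced split occurred. The trial is described as ongoing and the realised allocation is not reported.

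**What to change.** Replace simple randomisation with a single restricted draw. Once all four FMG and their participating physicians are enrolled, the independent biostatistician selects one of the six possible 2:2 allocations with equal probability and releases all four assignments together. This guarantees two FMG per arm, and concealment is kept because no assignment is known before the last FMG has joined.

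A block of four filled as FMG enrol is not a good substitute. The co-principal investigators contact FMG one after another, and once the first three assignments are known the fourth is predictable.

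The cost is one sentence in the protocol, a different setting in the randomisation software, and the wait for the fourth FMG before any can be assigned. The change does not make four clusters informative for hypothesis testing.

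If allocation has already taken place, state how it was done, report the number of FMG obtained in each arm, and specify restricted randomisation for the larger trial. If a draw of two out of four was what was meant all along, say so in place of the present wording.

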**Figure 2 F2:**
[figure not shown]
Decision+ Trial Design.

### Participants

#### Physicians

FPs/GPs are the main target participants and are recruited through FMG. A random list of all FMG in the Quebec City area was generated. Based on that list and in sequence, each physician who is in charge of the FMG is contacted by phone by one of the two co-principal investigators (FL or ML). If the contacted FMG includes at least 10 physicians, the study protocol is explained to the physician in charge and willingness to organise a meeting with colleagues from his/her group to further explain the nature of the project is sought.

FPs/GPs are not eligible to participate if they are currently participating or have previously participated to an implementation study of SDM in clinical practice. They are also excluded if they do not plan to be in clinical practice for the whole duration of the study (e.g. pregnancy, retirement, practice restricted exclusively to administrative duties). A FMG is not eligible if less than six eligible physicians agree to participate in the study. Reasons for exclusion or refusal to participate after the first telephone contact or after the face-to-face meeting are documented.

#### Patients

Patients are included if they meet the following criteria: a) adults or children consulting a participating physician for ARI, b) antibiotic treatment considered by the patient himself (or guardian) or by the physician, c) able (adults or guardians) to read, understand, and write French (equivalent to grade 8), and d) able to give informed consent (adults or guardians). Patients with a condition requiring emergency care are excluded. All participants, FPs/GPs and patients, sign an informed consent form approved by the ethics committee from the research institution.

#### Interventions

DECISION+ is a multifaceted CDP program offered over a 4- to 6-month period and includes the following:

#### Interactive workshops

Three 180-minute workshops are offered to participating FPs/GPs. Each one addresses a key component of our conceptual framework (Figure 1). The first workshop focuses on the probabilistic nature of the diagnosis of a bacterial vs. viral ARI. The second workshop focuses on the available evidence regarding the balance between risks and benefits when facing decision about the use antibiotics or not in ARI. It also addresses effective strategies to communicate this information to a patient. The third workshop focuses on strategies to foster active participation of patients in the decision-making process.

All three workshops include videos that facilitate group discussion about perceived barriers and facilitators to implementing SDM in the context of the use antibiotics for ARI. All workshops are offered at the FMG clinical site and leaded by experienced trainers (co-PI and co-I). Participants receive a toolkit including the material from the training workshops and a series of decision support tools to help them communicate with their patients the probability of a bacterial vs. viral ARI and the risks and benefits associated with the use of antibiotic in ARI. These decision support tools also include a section to help clarify patient's values regarding the use of antibiotics in ARI. All workshops are audio-taped to ensure fidelity of the intervention across FMG.

#### Reminders of expected behaviours

After completion of a given workshop, participating physicians receive reminders of the expected behaviours on a regular basis. The reminders summarize and emphasize the key elements of the workshops.

#### Feedback

Results of score agreement on the Decisional Conflict Scale between patients and physicians, as measured during the patient recruitment periods before the first workshop (Phase 1 in the experimental group and Phase 1 and 2 in the control group – see Figure 2), are provided to participating FPs/GPs in a personalized sealed envelope at the beginning of the third workshop. Physicians are also provided with pooled results from their colleagues. Time is provided during the workshop to explain how to interpret the results and for group discussion. A personalized and group prescription profile related to antibiotic prescribed to patients consulting with ARI is provided at the end of the series of workshops.

### Primary outcome measures

Primary outcome measures intend to assess the feasibility of a larger RCT aiming at evaluating the impact of the DECISION+ program. They include: a) proportion of contacted FMG that agree to participate, 2) proportion of recruited FPs/GPs that participate in the DECISION+ program, 3) level of satisfaction of FPs/GPs regarding DECISION+, and 4) proportion of missing data in each data collection phase. The subsequent RCT will be considered feasible if: 1) the proportion of contacted FMG that participate to the pilot study is 50% or greater, 2) the proportion of recruited physicians who participate in all three workshops is 70% or greater, 3) the mean level of satisfaction regarding the workshops is 65% or greater, and 4) the proportion of missing data in each completed questionnaire is less than 10%.

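### The missing-data go criterion counts only gaps inside completed questionnaires, and no go criterion covers patient recruitment, so the formal feasibility rule does not respond to unreturned forms or unfilled patient places.

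*Protocol article*

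**What the plan says.** Primary outcome measures lists four feasibility outcomes, the fourth being the "proportion of missing data in each data collection phase". The abstract gives the same definition. The section then sets four conditions under which the larger trial will be considered feasible:

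1. At least half of the FMG contacted take part in the pilot.
2. At least 70% of recruited physicians attend every one of the three workshops.
3. Average satisfaction with the workshops reaches at least 65%.
4. For missing data, "the proportion of missing data in each completed questionnaire is less than 10" per cent.

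In Background, the first specific aim is to "assess the feasibility of recruiting Family Medicine Groups (FMG), family physicians/general practitioners (FPs/GPs) and their patients". Sample size and analysis sets the patient target at "5 patients per physician in each one of the three recruitment phases", from at least 24 physicians and 360 patients in total. Data collection process says that patients and physicians are invited to complete the Decisional Conflict Scale after the encounter, and that patients are telephoned one to two weeks later for the Decisional Regret Scale.

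**The concern.** There are two separate gaps between what the pilot sets out to learn and what its decision rule measures.

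The first is a change of denominator. The outcome is defined over a phase; the criterion is defined over completed questionnaires. A form that never came back is not a completed questionnaire, so on the literal wording it adds nothing to the quantity tested. Whole-form loss is possible here, because the post-encounter scale is completed by invitation from two people and the regret scale depends on a later telephone call. A dyad agreement score needs both forms.

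The second is an aim without a criterion. Patient recruitment is named in the first aim and has a numerical target, but no threshold is tied to it.

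The decision to proceed to the larger trial is at stake. Dyad agreement on the Decisional Conflict Scale is a secondary outcome, and the Feedback section makes it part of the intervention, since physicians receive these results at the third workshop. A shortage of patients or complete dyads would affect both, and the go rule would not register it.

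**Working it through.** **Planned numbers.** Four FMG (Sample size and analysis), each with at least six participating physicians (Participants), give 4 × 6 = 24 physicians. Then 24 × 5 = 120 patients per phase and 120 × 3 = 360 in total. This reproduces the protocol's figure. Because the text says at least 24 physicians, 120 per phase is a minimum.

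**What each criterion depends on.** Criterion 1 uses FMG contacted and participating. Criterion 2 uses physicians recruited and workshops attended. Criterion 3 uses physicians' satisfaction ratings. None uses patient data. Criterion 4, read literally, uses only blank items within returned forms.

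**Formula.** Let q be the share of due forms returned by enrolled patients (or complete dyads) and m the share of items blank on returned forms.

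- Criterion 4 as worded tests m < 10%.
- Share of data due from enrolled patients that is absent = 1 − q × (1 − m).
- Recruitment = patients enrolled ÷ (5 × number of participating physicians), which enters no criterion.

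**One worked phase (all inputs except 120 are assumed; the protocol gives no expected rates).** 90 enrolled, 80 complete dyads, 65 regret calls completed, m = 3%.

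- Criterion 4 reads 3%: pass.
- Dyads absent: (90 − 80)/90 = 10/90 = 11%.
- Regret scores absent: (90 − 65)/90 = 25/90 = 28%.
- Adding blank items: dyads 1 − (80/90) × 0.97 = 14%; regret 1 − (65/90) × 0.97 = 30%.
- Recruitment: 90/120 = 75% of the minimum.

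**Range.** Share of data due from enrolled patients that is absent, for assumed q and m. Criterion 4 passes in every cell:

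| Return q | m = 0% | m = 5% | m = 9% |
|---|---|---|---|
| 100% | 0.0% | 5.0% | 9.0% |
| 80% | 20.0% | 24.0% | 27.2% |
| 60% | 40.0% | 43.0% | 45.4% |

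Even with no blank items, a 10% limit on this denominator is reached at q = 90%. Recruitment changes none of these cells: the criterion 4 reading is the same with 360 patients or 180.

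**The case against.** Four points can be made for the protocol.

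- **Loose reading.** Outcomes and criteria are listed in the same order, so criterion 4 may be meant as the threshold for outcome 4, with the phrase about completed questionnaires standing for each type of questionnaire administered. This is possible. It would make the first half of the point an ambiguity to clarify. It would not bring in patients who were never recruited.
- **The gaps need not be hidden.** A reader might infer that the pilot would conceal non-response. The documents do not support that. Outcome 4 is itself a primary outcome defined per phase, primary outcomes are to be reported with 95% confidence intervals, and a shortfall against 360 patients would be visible. The fault lies in the formal rule only.
- **Size.** A reader might divide by planned patients and say that 40/120 = 33% of dyads and 55/120 = 46% of regret scores are missing in the worked phase. That merges unfilled places with non-response among enrolled patients. The two need separate measures, and on the enrolled denominator the figures are 11% and 28%. All of them rest on assumed rates.
- **Importance.** Which aspects of feasibility receive a numerical threshold is partly a design choice. The protocol does not rank threats to the larger trial, so it cannot be said from the documents that patient recruitment and non-response are the main ones. This is a four-FMG pilot, and the issue touches no participant's care and no effect estimate.

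These points limit the severity. They do not remove the mismatch between outcome and criterion, or the absence of any criterion for a stated part of the first aim.

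**Conclusion.** The point holds in a limited form and should be fixed, though it does not invalidate the pilot. The go rule is fully stated in the article, so this is not a detail left to another document. On its literal wording, criterion 4 does not respond to unreturned forms or missed calls, and on any wording the four criteria do not respond to patient recruitment. Provided criteria 1 to 3 are met and blank items stay under 10%, the larger trial is declared feasible at any rate of recruitment or return.

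That insensitivity follows from the text and needs no assumption. The sizes do: in the worked phase, an 11% loss of dyads, a 28% loss of regret scores and 75% recruitment all coexist with a pass at 3%. It cannot be concluded that the pilot will in fact reach a wrong decision, because the documents give no expected recruitment or return rates.

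**What to change.** **(a) Restate criterion 4 to match the outcome.** In each phase, take as denominator all questionnaires due from enrolled patients and their physicians, including the regret call. Count unreturned forms and uncompleted calls as missing, and report blank items either separately or in the same figure, saying which. The sponsor should confirm that 10% is the intended limit on this wider denominator; it should not be carried over by default, because the test becomes stricter.

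**(b) Add a go criterion for the patient part of the first aim.** In each phase, patients recruited divided by five times the number of participating physicians. The denominator is at least 120 and rises with more physicians, so 120 should not be written in as a fixed target. The sponsor sets the threshold before the feasibility results are examined. Background describes the pilot as ongoing, so a dated note should record when the change was made and what had been seen by then.

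**Cost.** One reworded criterion and one new one, using counts of patients enrolled, forms due and forms returned. The feasibility test becomes harder to pass and the reported figure less favourable. Revising go criteria during a study carries its own risk, which the dated note is meant to contain.
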